### **6.5.3 Regulatory reporting requirements for serious adverse events**

The investigator will promptly report all SAEs to EMVI and in case of AS02 to GSK in accordance with the procedures detailed in Section 6.5.2. EMVI and GSK Biologicals have a legal responsibility to promptly notify, as appropriate, both the local regulatory authority and other regulatory agencies about the safety of a product under clinical investigation. Prompt notification of SAEs by the investigator to the Study Contacts for Reporting SAEs is essential so that legal obligations and ethical responsibilities towards the safety of other subjects are met.

The investigator, or responsible person according to local requirements, will comply with the applicable local regulatory requirements related to the reporting of SAEs to regulatory authorities and the IRB/IEC.

Expedited Investigator Safety Reports (EISR) are prepared according to EMVI and GSK Biologicals policy and are forwarded to investigators as necessary. An EISR is required for:

- development compounds (i.e. compounds not marketed), if the event is serious, unexpected and has a suspected relationship to study drug treatment. Expected adverse events for development compounds will be described in the Development Core Safety Information (DCSI) in the Investigator Brochure (IB).
- The purpose of the EISR is to fulfil specific regulatory and Good Clinical Practice (GCP) requirements, regarding the product under investigation.
- An investigator who receives an EISR describing a SAE or other specific safety information from EMVI or GSK Biologicals will file it with the Investigator Brochure and will notify the IRB/IEC, if appropriate according to local requirements.

[figure not shown]

#### **6.5.4 Post study adverse events and serious adverse events**

A post-study AE/SAE is defined as any event that occurs outside of the AE/SAE detection period defined in Section 6.3.3. Investigators are not obligated to actively seek AEs or SAEs in former study participants.

However, if the investigator learns of any SAE, including a death, at any time after a subject has been discharged from the study, and he/she considers the event reasonably related to the investigational product, the investigator will promptly notify the Study Contact for Reporting SAEs.

#### **6.6 Pregnancy**

Subjects who become pregnant during the study (one month after the first dose or three months after the second dose) must not receive additional doses of study vaccine but may continue other study procedures at the discretion of the investigator.

The investigator, or his/her designee, will collect pregnancy information on any subject who becomes pregnant while participating in this study. The investigator, or his/her designee, will record pregnancy information on the Pregnancy Report Form and submit it to EMVI and GSK within 24 hours of learning of a subject's pregnancy, regardless of the adjuvant used. The investigator will inform the safety monitor as soon as possible. The safety monitor will break the code for the pregnant subject and inform GSK and EMVI about the adjuvant used. The investigator will remain to be blinded.

The subject will be followed to determine the outcome of the pregnancy. At the end of the pregnancy, whether that be full-term or prematurely, information on the status of the mother and child will be forwarded to EMVI and GSK. Generally, follow-up will be no longer than six to eight weeks following the estimated delivery date.

While pregnancy itself is not considered an AE or SAE, any pregnancy complication or elective termination of a pregnancy for medical reasons will be recorded as an AE or a SAE, as described in Section 6.3 and 6.4, and will be followed as described in Section 6.5.

A spontaneous abortion is always considered to be a SAE and will be reported as described in Section 6.5. Furthermore, any SAE occurring as a result of a post-study pregnancy AND considered reasonably related in time to receipt of the investigational product by the investigator, will be reported to EMVI and GSK Biologicals as described in Section 6.5.4. While the investigator is not obligated to actively seek this information from former study participants, he/she may learn of a pregnancy through spontaneous reporting.

Information on pregnancies identified during the screening phase/prior to vaccine administration does not need to be collected; this information need not be communicated to safety.

[figure not shown]

## **6.7 Treatment of adverse events**

Treatment of any adverse event is at the sole discretion of the investigator and according to current good medical practice. Any medication administered for the treatment of an AE should be recorded in the subject's CRF.

## **6.8 Loss to follow-up Procedures**

If a subject fails to appear for a follow-up examination, extensive effort (i.e., documented phone calls and certified mail) should be undertaken to locate or recall him/her or at least to determine his/her health status. These efforts should be documented in the subject's CRF and source documents.

# **7 EVALUATION CRITERIA**

## **7.1 Primary Evaluation Criterion : Safety**

### **7.1.1 Definition of the Criterion**

The safety profile will be assessed on the following criteria

- Immediate reactogenicity; defined as any systemic adverse reactions occurring within 30 minutes after each injection,
- Local and systemic reactogenicity measured from day 0 to day 14 after each dose
- Any unsolicited adverse event resulting in a visit to a physician between each injection and one month after the third dose.
- Any Serious Adverse Event (SAE) occurring from the inclusion through out the study. The relationship of the adverse event to the study vaccine will be established by the investigator, using the following definitions : related or not related.
- Biological safety, one month after each vaccination, in reference with the baseline before the first dose, by measuring the following :
  - RBC, hemoglobin, hematocrit, MCV, MCH, MCHC, platelets, WBC with differential counts
  - Potassium, sodium, ASAT, ALAT, total bilirubin, alkaline phosphatase,  $\gamma$ GT, creatinin

### **7.1.2 Parameters to be measured**

The rate, duration and severity of signs and symptoms during the 14 days after the immunization will be measured.

#### **1. Local reactions**

The following local reactions will be recorded during the 14 days following the vaccination (D0 and D14 follow-up) :

##### **1. Any local**

[figure not shown]

2. **Pain** : Intensity and duration
3. **Redness** : Size (mm) and duration
4. **Swelling**: Size (mm) and duration
5. **Other Local** : Intensity or size and duration

## 2. *Systemic reactions*

The following systemic reactions will be recorded immediately after the injection (30 minutes) and during the 14 days following the vaccination (D0 and D14 follow-up):

1. **Any systemic**
2. **Fatigue** : Duration and intensity
3. **Fever** : Intensity and duration
4. **Headache** Intensity and duration
5. **Malaise**: Intensity and duration
6. **Myalgia**: Intensity and duration
7. **Joint pain**: Intensity and duration
8. **Gastro-intestinal symptoms**:
  - **Nausea**: Intensity and Duration
  - **Diarrhoea** : Intensity and Duration
  - **Vomiting** : Intensity and Duration
  - **Abdominal pain**: Intensity and Duration
9. **Contro-lateral local reaction** : Intensity and Duration
10. **Other systemic** : Intensity and Duration

### 7.1.3 Method and Timing of Measurement

#### 1. *Local reactions*

The duration of the **pain** will be measured in minutes, hours or days, and the severity scale as 1) mild: easily tolerated, does not interfere with daily life 2) moderate: discomfort that interferes with or limits usual daily activity 3) severe: disabling, inability to perform usual daily activity, including a functional limitation of the movement.

The duration of redness, swelling, and other local reaction will be measured in hours or in days.

The size of redness, swelling, will be measured in cm with a rule, the maximum length will be reported on the CRF, in mm. **Redness, or swelling**. of less than 20 mm is mild, of 20-50 mm is moderate, and of greater than 50 mm is severe

Solicited local reactions will be recorded at visits V2; V3, V4; V5, V6, V, V8, V9, V10, V11, V13, V14, V15, V16 and V17. The subjects will report daily the local reactions in their diary from day 1 to day 14 after the vaccination.

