## FLOW CHART

**Prime & Boost phase, 19 Visits, 3 Vaccinations, Randomised, Dose Escalating, 365 Days duration/subject**

| Visit Number                    | V1                                          | V2              | V3               | V4         | V5         | V6              | V7               | V8            | V9         | V10        | V11             | V12               | V13                  | V14            | V15         | V16         | V17             | V18              | V19           |
|---------------------------------|---------------------------------------------|-----------------|------------------|------------|------------|-----------------|------------------|---------------|------------|------------|-----------------|-------------------|----------------------|----------------|-------------|-------------|-----------------|------------------|---------------|
| Trial Timelines (Days,)         | D-28                                        | D0              | D1               | D3         | D7         | D14             | D28              | D29           | D31        | D35        | D42             | D56               | D112                 | D113           | D115        | D119        | D126            | D140             | D365          |
| Time Windows (Days or Hours)    |                                             | ± 7 D           | ± 6 hrs          | ± 24 hrs   | ± 24 hrs   | ± 2 D           | ± 2 D            | ± 6 hrs       | ± 24hrs    | ± 24 hrs   | ± 2 D           | ± 2 D             | ±7 D                 | ± 6 hrs        | ± 24hrs     | ± 24 hrs    | ± 2 D           | ± 2D             | ± 14 D        |
| Visit Intervals                 |                                             | V1
+4
wks | V2
+24
hrs | V2
+ 3D | V2
+ 7D | V2
+2
wks | V4
+ 2
wks | V7
+ 24hrs | V7
+ 3D | V7
+ 7D | V7
+2
wks | V11
+ 2
wks | V7
+12wks         | V13
+ 24hrs | V13
+ 3D | V13
+ 7D | V9
+2
wks | V11
+2
wks | V1
+1 year |
| Vaccination Doses               |                                             | Vac1     |                  |            |            |                 | Vac2      |               |            |            |                 |                   | Vac3          |                |             |             |                 |                  |               |

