| Contra- Indications Review      |                                             | X               |                  |            |            |                 | X                |               |            |            |                 |                   | X                    |                |             |             |                 | X                |               |
| Pregnancy Test                  | X                                           | X               |                  |            |            |                 | X                |               |            |            |                 |                   | X                    |                |             |             |                 |                  |               |
| Immediate surveillance (30 min) |                                             | X               |                  |            |            |                 | X                |               |            |            |                 |                   | X                    |                |             |             |                 |                  |               |
| Solicited Events                |                                             |                 | X                | X          | X          | X               |                  | X             | X          | X          | X               | X                 |                      | X              | X           | X           | X               |                  |               |
| Unsolicited Events              |                                             | X               | X                | X          | X          | X               |                  | X             | X          | X          | X               | X                 |                      | X              | X           | X           | X               |                  |               |
| Serious adverse events          | To be reported at any time during the trial |                 |                  |            |            |                 |                  |               |            |            |                 |                   |                      |                |             |             |                 |                  |               |

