### **6.2.3 Review of Safety Data by the Safety Monitor**

Vaccinations are scheduled every month. Reactogenicity and safety evaluations will be collected over a period of 14 days (day of vaccination and subsequent 13 days after each vaccination) after each vaccination. The following events must occur within the specified timeframe to ensure proceeding to the next vaccination as per schedule.

The data manager must generate a summary of all reactogenicity reported by subjects during the 14 days follow-up period after vaccination and also any safety laboratory values outside the normal ranges. This report will be sent to the Safety Monitor and EMVI monitor by Day 19.

The Safety Monitor and EMVI monitor must review the safety data for each subject within 2 business days and if warranted instruct the site and the sponsor to withdraw individual subjects and/or suspend further vaccination, at least 4 business day prior to the next vaccination.

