#### 2. *Systemic reactions*

The duration in hours or in days of all systemic reaction will be monitored by the investigator, as well as the time interval of occurrence after the last vaccination.

Oral temperature will be measured with a thermometer and the intensity of **fever** will be defined as 1) mild when comprised between 37°,5°C and 38°C, 2) moderate when comprised between 38°C and 39,0°C and 3) severe when > 39,0°C.

[figure not shown]

The systemic reactions will be monitored at visits V2; V3, V4; V5, V6, V7, V8, V9, V10, V11 and V12. The subjects will report daily the systemic reactions in their diary from day 0 to day 14 after the vaccination.

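### The local-reaction diary starts on day 1, although the primary reactogenicity criterion and the systemic entries in the same diary start on day 0

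*Protocol*

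**What the plan says.** - **Primary criterion.** Section 7.1.1 (and the synopsis) lists "Local and systemic reactogenicity measured from day 0 to day 14 after each dose". Section 7.1.2 also labels the local follow-up as D0 and D14.
- **Local diary.** Section 7.1.3, local reactions: "The subjects will report daily the local reactions in their diary from day 1 to day 14 after the vaccination".
- **Systemic diary.** Section 7.1.3, systemic reactions: "The subjects will report daily the systemic reactions in their diary from day 0 to day 14 after the vaccination".
- **Clinic recording.** Section 7.1.3 begins its list with "Solicited local reactions will be recorded at visits V2; V3, V4; V5, V6" and goes on to include V13. A stray V between V6 and V8 is probably V7. The flow chart row "Solicited Events" has no mark at V2, V7 or V13; its first marks after each dose are at V3, V8 and V14.
- **Immediate observation.** The criterion in 7.1.1 is "Immediate reactogenicity; defined as any systemic adverse reactions occurring within 30 minutes after each injection", so it is defined for systemic reactions only. Section 6.3.2 is broader: it asks for local as well as systemic reactions, immediate ones included, with date and time of occurrence, duration and intensity.
- **Status of the diary.** Section 3.3.2 makes the diary the source document for the 14 days after each injection. It is handed out at the vaccination visit, with a ruler for daily measurement.
- **Safety review.** Section 6.2.3 uses the vaccination day plus 13 further days.

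**The concern.** The instruction for collecting local reactions does not match the window of the criterion it serves. Section 6.3.1 expects local reactions and describes systemic ones as less often observed, yet only the systemic entries cover the vaccination day. Section 7.1.2 classes a contralateral local reaction as systemic. Taken literally, then, the uninjected arm has a day 0 diary entry and the injected arm has none.

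At stake is the same-day record of local reactions in the hours after the subject goes home. Section 7.1.2 makes rate, duration and severity the parameters, and 7.1.3 allows pain to last minutes or hours, so short reactions are in scope. An entry not made that evening cannot be reliably reconstructed later.

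**Working it through.** The protocol gives no figure to reproduce. The check compares the windows and counts inclusive days (last day − first day + 1).

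| Source | Window | Days per dose |
|---|---|---|
| 7.1.1 primary criterion | day 0 to 14 | 14 − 0 + 1 = 15 |
| 7.1.3 systemic diary | day 0 to 14 | 14 − 0 + 1 = 15 |
| 7.1.3 local diary | day 1 to 14 | 14 − 1 + 1 = 14 |
| 6.2.3 safety review | day 0 to 13 | 13 − 0 + 1 = 14 |

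**Can day 1 mean the vaccination day?** No. The flow chart sets V2 at D0 and V3 at D1, 24 hours later.

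**Number of entries.** One per dose × 3 doses = 3 per subject. For 60 subjects who all receive 3 doses, 60 × 3 = 180.

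**When is the next scheduled look?** V3, V8 and V14 are each 24 hours after the vaccination visit, with a window of ± 6 hours. That gives 24 − 6 = 18 hours to 24 + 6 = 30 hours.

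**What fills the interval?** Recording at V2 and V13 under 7.1.3 can cover only the time on site, and the flow chart does not schedule it. After that, only the diary gives a same-day record, and its local part starts the next day.

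**Does the far end of the window hold?** The day 14 visits are V6 (D14), V11 (D42 = 28 + 14) and V17 (D126 = 112 + 14). The flow chart collects the first two cards at V6 and V11, but the third at V16 (D119), which is 119 − 112 = 7 days after dose 3. Days 8 to 14 of dose 3 would then have no card. Section 3.3.2 says the diaries are collected on day 14 but names V4 (D3), V7 (D28) and V11 (D42); only V11 is a day 14 visit. Correcting the first day alone would not secure a day 0 to 14 window at dose 3.

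**The case against.** The strongest reply is that the diary sentence is an isolated slip and that day 0 is covered elsewhere. Section 6.3.2 requires immediate local reactions to be documented, with date and time, whether the investigator or the subject observed them. Section 7.1.3 names V2 and V13, and a clinic visit follows within 30 hours. Section 3.3.2 describes one diary for local and systemic reactions, already in the subject's hands on day 0. The card itself is not shown, so it may have a day 0 local field. Redness and swelling are reported as the maximum extent, so peak grade changes only if a reaction peaks that evening, subsides before the next visit and is not reported there.

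Most of this stands. A reader might infer that vaccination-day local data are missing altogether; 6.3.2 and the visit list in 7.1.3 do not support that. What is lost is recording at the time, with recall as the fallback.

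A reader might also infer that the hold rule in 6.2.2, which needs Grade 3 to persist for more than 48 hours, is weakened. That would follow only if persistence were read from daily diary entries. Section 6.3.2 asks for date and time of occurrence, section 6.3.3 for a new record when intensity changes, and no time of day is set for the diary, so no loss in hours can be established.

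Nor does the day 13 end of the review window have a shown consequence. It is a separate window from the criterion, and 6.2.3 itself goes on to speak of a 14-day follow-up.

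**Conclusion.** The inconsistency is real and lies in operative text, but it is minor. The local diary is one day of 15 short at each dose, and the missing day is the vaccination day. Local reactions after the subject leaves the clinic then depend on recall at 18 to 30 hours. The likely effect is on recorded onset, on duration, and on any early peak that subsides before that visit. Its size cannot be derived from the protocol: the share of calendar days does not measure bias, and no frequency of such short-lived reactions is given.

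The conclusion assumes that the diary card follows 7.1.3 as written. The count of 180 further assumes that all 60 subjects receive all three doses.

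**What to change.** - **Section 7.1.3:** start the local diary on day 0, the evening of vaccination, as the systemic entries already do. Replace the stray V in the visit list by V7, if that is what is meant.
- **Flow chart:** mark solicited events at V2, V7 and V13.
- **Section 6.2.3:** state the review window as day 0 to 14, for consistency only.
- **Diary collection:** set it to V6, V11 and V17 in both 3.3.2 and the flow chart, so that the window also holds at dose 3.

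The hold rule in 6.2.2 needs no change on this account. The cost is a few words in each place and one extra local diary entry per dose, 3 per subject. The card and ruler are already provided and V17 is already scheduled, so no visit, sample or form is added.

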#### 2. *Systemic reactions*

The duration in hours or in days of all systemic reaction will be monitored by the investigator, as well as the time interval of occurrence after the last vaccination.

Oral temperature will be measured with a thermometer and the intensity of **fever** will be defined as 1) mild when comprised between 37°,5°C and 38°C, 2) moderate when comprised between 38°C and 39,0°C and 3) severe when > 39,0°C.

[figure not shown]

The systemic reactions will be monitored at visits V2; V3, V4; V5, V6, V7, V8, V9, V10, V11 and V12. The subjects will report daily the systemic reactions in their diary from day 0 to day 14 after the vaccination.

## **7.2 Secondary Evaluation Criteria : Immunogenicity**

The immunogenicity of the different formulation of the vaccine will be assessed on the level and the quality of circulating antibodies as well as the stimulation of the T-cell immune response.

### **7.2.1 Humoral Immune response**

#### **1. Definition**

**The humoral response** to the vaccine antigens will be assessed by measuring the level of IgG, before each vaccination, one month after each vaccination and one year after the first vaccination.

An IFA for at least two parasite strains will be employed to verify that the antibodies elicited by the vaccine recognise the native protein on merozoites.

•

#### **2. Parameters to be Measured, Method and Timing of Measurement**

IgG titres will be measured by ELISA. In the event IgG titres are undetectable, additional IgM ELISA's will be performed.

The level of IgG will be expressed in concentration ( $\mu\text{g/mL}$  of AMA-1-specific IgG antibody, calculated from a calibrated reference human pool serum provided by [name]).

The ELISA for IgG titres will be performed at samples obtained at D0, D28, D56, D112, D140 and D365.

An IFA, with at least 2 parasite strains will be performed at D0 and D140. The antibody to be detected in the IFA will be IgG.

These tests will be performed by the Radboud University Nijmegen Medical Center.

### **7.2.2 Cellular Immune response:**

#### **1. Definition:**

The cellular immune response to the vaccine antigen will be assessed by measuring T cell proliferation and cytokine production by ELISPOT following in vitro stimulation.

